
**Figure 1 F1:**
[figure not shown]
Flow chart for obtaining 200 ml of peritoneal fluid.

**Table 1 T1:** Subject inclusion criteria.

• Patient age 18 years or older, both sexes. • Clinical diagnosis of primary gastrointestinal or gynecologic malignancy. • Patient must be planning to undergo complete resection of all primary tumor. • ECOG performance status of less than or equal to 1. • Hematology: ANC greater than or equal to 1500/µl. • Platelets: greater than 75 000/µl. • Adequate renal function: creatinine less than 1.5× the upper limit of normal (ULN) or calculated creatinine clearance of greater than or equal to 50 ml/min. • Adequate hepatic function: bilirubin less than 1.5 mg/dl (except in patients with Gilbert’s syndrome, who must have a total bilirubin <3.0 mg/dl). • Women of childbearing potential with a negative pregnancy test result (urine or blood) who agree to use an effective contraceptive method. Reliable contraception should be used from trial screening and must be continued throughout the study. A woman of childbearing potential is defined as one who is biologically capable of becoming pregnant. • A man participating in this study must agree to utilize a reliable barrier form of contraception for the duration of the study. • Signed and dated written informed consent to participate in this clinical trial must be obtained prior to any study procedure.

**Table 2 T2:** Subject exclusion criteria.

• Subjects who have previously undergone intraperitoneal chemotherapy. • Subjects with preoperative or intraoperative biopsy consistent with peritoneal metastases or disseminated disease. • Other prior malignancies, except for cured non-melanoma skin cancer, curatively treated *in situ* carcinoma of the cervix, adequately treated malignancies for which there has been no evidence of activity for more than three years, or indolent tumors for which observation over 2 years is a reasonable option. • High suspicion for extra-abdominal metastases. • Women who are pregnant or lactating. • Subjects with a condition which may interfere with their ability to understand the requirements of the study. • Active coronary artery disease (defined as unstable angina or a positive cardiac stress test). Subjects with a history of coronary artery disease may be included if they have had a normal stress test within 60 days of enrollment or are determined by a cardiologist to be of acceptable perioperative risk. • Uncontrolled hypertension defined as greater than 140/90 and not cleared for surgery at the time of consent. • New York Heart Association (NYHA) Class II or higher congestive heart failure; restrictive or obstructive pulmonary disease that would limit study compliance or place the patient at unacceptable risk for participation in the study. • History of cerebrovascular disease that would limit study compliance or place the patient at unacceptable risk for participation in the study. • Subjects with other concurrent severe medical problems unrelated to the malignancy that would significantly limit full compliance with the study or place them at unacceptable risk for participation in the study. • Patients with known cisplatin, carboplatin, or pemetrexed allergy. • Evidence of extensive intraperitoneal adhesions at the time of surgery, which prohibits intraperitoneal therapy, as determined by the operating surgeon. • Any condition that would preclude the ability to deliver appropriate intraperitoneal chemotherapy. • Use of an oral medication, lacking a suitable nonoral substitute, that if held for up to 10 days would be felt an unacceptable risk by the investigator. • Life expectancy less than 12 weeks.

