**Materials and methods::**

The result of this test is to be available at or before the completion of the cancer resection. If the cytology is positive, the patient immediately becomes a candidate for HIPEC. The HIPEC will be of maximal value if a complete cytoreduction, as judged by the surgeon, has been possible. This phase 1 trial is to demonstrate that the Surgical Oncology Service, the Department of Pathology, the Pharmacy and the Operating Room personnel can co-ordinate a phase 1 protocol to successfully complete the same day cytology with an efficient delivery of HIPEC. A standardized plan for consent, cytology collection, preparation of the specimen, reading of the specimen, reporting the results in a timely manner facilitates the administration of HIPEC in peritoneal cytology positive patients.

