## Methods/design

### Objectives

The goal of this study is to demonstrate the feasibility of a same day cytology to select patients with a complete cancer resection for HIPEC. In order for this strategy to be successful the Surgical Oncology Service, the Department of Pathology/Cytology, the Hospital Pharmacy, and the Operating Room personnel must provide a coordinated effort.

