### Methods

A first requirement is preoperative consent for HIPEC in gastrointestinal and gynecologic malignancy patients having abdominal-pelvic surgery for cancer (Tables 1, 2). Patients with a primary or recurrent cancer will require not only a standard consent for complete resection of the malignancy but also consent for HIPEC.The surgical procedure scheduled with the operating room must also include collection of the same day cytology specimen and possible administration of HIPEC. In order to avoid unnecessary delay, the equipment required for same day cytology must be available prior to the start of the surgical procedure. Also, the administration of the standard HIPEC for gastrointestinal or gynecologic malignancy must be possible with a few minutes notice.Collection of the same day cytology specimens: The same day cytology specimen is to be collected just after access to the abdomen and pelvis has been obtained (Fig. 1). Adhesions should be lysed to gain visual access to the right upper quadrant, right paracolic sulcus, left paracolic sulcus, and deep pelvis. An exploration of the abdomen and pelvis with a full description of the findings should be recorded in the operative note dictated by the surgeon. Prior to collection of the same day cytology specimen lysis of adhesions or surgical dissection that results in bleeding must be avoided. A bloody same day cytology specimen is more difficult to read. Also, blood contaminates the peritoneal fluid and will dilute the number of malignant cells identified.Four specimens of 50 ml each are to be obtained from each patient. If the patient has ascites no saline irrigation is required. Forcibly instill 50 ml into the right upper quadrant (superior and inferior to the liver), into the right paracolic sulcus, into the left paracolic sulcus, and into the deep pelvis posterior to the rectum. If the peritoneal fluid collection from each anatomic site is not equal to 50 ml, instill the volume of saline needed to provide a 50 ml specimen. The aspirations each containing 50 ml, should be contained in a suction container dedicated to the recovery of 200 ml of peritoneal fluid aspirate. It should leave the operating room table and be handed off to go to the cytology laboratory (800 cc Suction Canister, Cardinal Health Inc.).One of the assumptions of this phase 1 study is that a lavage of four anatomic sites at the time of the exploration of the abdomen and pelvis in a surgical procedure produces a higher likelihood of a positive result that a paracentesis. If same day cytology is available, it can simplify patient management and reduce the incidence of false negative peritoneal cytology.Preparation of the same day cytology specimen for the pathologist/cytologist: The 200 ml suction container is handed off the operating table, immediately uncapped and 500 units of heparin added. The 200 ml suction container is swirled to disperse the heparin. The 200 ml of peritoneal irrigation fluid or ascites are transferred to the Pathology/Cytology Department. Tubes containing the peritoneal fluid are centrifuged at 2000 rpm for 10 min. The fluid is suctioned off taking care to preserve the cellular pellet at the base of each tube. The cellular pellets from three tubes are agitated by pipette and transferred to the fourth tube. This tube is recapped, centrifuged, and transferred to the pathologist/cytologist for staining and reading.Staining and reading of the same day cytology specimen: A portion of the sediment is smeared on four glass slides. Two slides should be smeared with ~1 ml of sediment and prepared for microscope study by the Papanicolaou thin prep method. Two slides should be smeared with ~1 ml of sediment and allowed to air dry. They will be prepared for microscope study by the Diff Quick method. The remainder of the cellular pellet is submitted for cell block. Hematoxylin and eosin stain and appropriate immunostains for the malignancy being treated will supplement the same day cytology report several days later.Interpretation of the slides for same day cytology: A slide should be interpreted as positive if clusters of or individual cells are detected. For an experienced cytopathologist differences between cancer cells and reactive mesothelial cells should be apparent.Time allowed for the final report for the same day cytology: The primary goal of this pilot study is to demonstrate the feasibility and reproducibility of the same day cytology. To be successful the results of the cytology must be available when the cancer specimen is removed. A 3 h time allowed for the final report of the same day cytology is required. Early reporting is of benefit in that preparation for HIPEC will be facilitated.Standard HIPEC for positive same day cytology: If the same day cytology is positive a standardized HIPEC regimen is performed. The HIPEC methodology may be open or closed at the discretion of the surgical oncology team. The chemotherapy agents to be used are selected by the peritoneal surface malignancy team. The HIPEC treatment is maintained for 90 min at 42°C in the whole abdomen and pelvis.Review of slides obtained by same day cytology: All slides will be stored for consultation within a group meeting of pathologists/cytologists from all participating institutions. A record of positive cytologies by digital photography is recommended. All negative slides will be reviewed to assess the quality of the staining technology.Accrual: The plan is to continue the study until 20 positive same day cytology reports with HIPEC administered have been achieved. The total number of patients in the feasibility trial cannot be estimated at this time.Future plans: A randomized trial to test the efficacy of HIPEC in patients with positive same day cytology is planned.Ethics approval and consent to participate from patients for this study will be obtained.

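### Table 2 makes inability to deliver intraperitoneal chemotherapy an exclusion even when found at surgery, so untreated cytology-positive patients can leave the delivery count as ineligible

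*Protocol article*

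**What the plan says.** The Abstract (Materials and methods) says the trial is to show that the services involved can "successfully complete the same day cytology with an efficient delivery of HIPEC". The Objectives section adds: "The goal of this study is to demonstrate the feasibility of a same day cytology to select patients with a complete cancer resection for HIPEC".

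On timing, Table 1 requires: "Signed and dated written informed consent to participate in this clinical trial must be obtained prior to any study procedure". The Methods section then states: "The same day cytology specimen is to be collected just after access to the abdomen and pelvis has been obtained".

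Three items in Table 2 (Subject exclusion criteria) matter here:
- The adhesion item: "Evidence of extensive intraperitoneal adhesions at the time of surgery, which prohibits intraperitoneal therapy, as determined by the operating surgeon"
- The biopsy item: "Subjects with preoperative or intraoperative biopsy consistent with peritoneal metastases or disseminated disease"
- The untimed deliverability item: "Any condition that would preclude the ability to deliver appropriate intraperitoneal chemotherapy"

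Under Accrual, the Methods section continues the study until 20 positive reports with HIPEC given have been reached, and says that the total number of patients cannot be estimated.

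**The concern.** An exclusion criterion normally settles who enters the study. Here two items concern whether HIPEC can be delivered. One is explicitly a finding at surgery, and the other carries no time limit. Delivery of HIPEC after a positive result is part of what the study sets out to show, so failure to deliver is an outcome of interest. If the same failure is also grounds for exclusion, delivery among positives is conditioned on delivery having been possible.

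A feasibility result built this way could support the planned randomized trial with a delivery rate better than a new site would see. It would also hide how often, and why, a positive result cannot be acted on, which a feasibility study is well placed to record.

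**Working it through.** **Step 1. Order of events.** Consent comes before any study procedure (Table 1). Abdominal access follows, then the specimen (Methods, collection of specimens). The report is allowed 3 h and should be available when the cancer specimen is removed. HIPEC follows if the cytology is positive and resection is complete (Goals of this protocol).

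**Step 2. When each Table 2 item can be met.**

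| Item | Before consent | After consent | After sampling |
|---|---|---|---|
| Adhesions at surgery that rule out intraperitoneal therapy | No | Yes, always | Possible; may be seen at access |
| Any condition precluding delivery | Yes | Yes, no time limit | Possible |
| Biopsy, preoperative limb | Yes | Possible | No |
| Biopsy, intraoperative limb | No | Yes, always | Often |

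The Methods section itself expects adhesions to be dealt with around the time of sampling: "Adhesions should be lysed to gain visual access to the right upper quadrant, right paracolic sulcus, left paracolic sulcus, and deep pelvis". The adhesion finding may therefore come shortly before or after the specimen is taken.

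**Step 3. Which items overlap with the study question.** The first two are about deliverability and overlap directly with the aim in the Abstract and Objectives. The biopsy item is different. It removes patients with gross peritoneal metastases, which partly defines the population the study is meant for.

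**Step 4. How the article handles a parallel case.** Complete resection is also known only at surgery. Table 1 requires only that it be planned, and Goals of this protocol makes actual completeness a condition for giving HIPEC. A patient whose resection proves incomplete stays in the study and is simply not a candidate. Deliverability is not handled this way.

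**Step 5. Size, by illustration.** The only stated figure is the accrual target of 20 treated positives. It is a fixed count. The article gives no error rate, power or success threshold from which to reproduce it.

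Let *k* be the number of cytology-positive patients not treated because of a Table 2 deliverability item. The documents do not give *k*, so a range is assumed. Delivery among all positives is 20/(20 + *k*):
- *k* = 0: 20/20 = 100% (exact 95% CI 83.2 to 100)
- *k* = 2: 20/22 = 90.9% (70.8 to 98.9)
- *k* = 5: 20/25 = 80.0% (59.3 to 93.2)
- *k* = 10: 20/30 = 66.7% (47.2 to 82.7)

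The intervals treat the denominator as fixed. Accrual actually stops on treated patients, so they are a rough guide. If the *k* patients are removed as ineligible and no positive patient misses HIPEC for another reason, every row reads 20/20.

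**The case against.** The strongest reply is that the article states no delivery-rate endpoint, no analysis set and no rule discarding data from patients excluded at surgery. Such matters are usually left to the full protocol or analysis plan, which could keep these patients in. The untimed item sits near allergy, oral-medication and life-expectancy items that can be judged before surgery, and may be meant as a preoperative catch-all. Failures of coordination, such as a late report or an unprepared drug, are not naturally patient conditions, so Table 2 would not clearly remove them. The accrual target already counts only treated patients.

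Much of this stands, and it rules out several stronger readings a reader might infer:
- **All three items can be met only after sampling.** This is wrong for the untimed item and for the preoperative limb of the biopsy item, and not certain for adhesions.
- **The trial would report 20/20.** No text says so; it depends on removal and on no other cause of non-delivery.
- **Turnaround times are biased toward success.** Excluded patients might be lost from those data, but nothing shows that their times would be longer.
- **The surgeon excludes knowing the cytology result.** The timing allows it, but for adhesions seen early it is unlikely, and the article does not address it.
- **A biopsy result could exclude a patient days after HIPEC.** The article does not say how the biopsy is read.

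What the reply does not remove is the eligibility table itself. Table 2 is stated text, and an explicitly intraoperative bar to intraperitoneal therapy is listed there as a subject exclusion. A later analysis set defined on eligible patients would inherit that, even with a fixed total number of patients, so the point is separate from the accrual rule.

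**Conclusion.** The concern holds in a limited form. Applied after consent, the two deliverability items in Table 2 can turn a cytology-positive patient who could not be treated into an ineligible one. The delivery proportion among positives may then look too favourable. The intraoperative limb of the biopsy item can also act after consent and often after sampling, but it partly defines the target population and is not in itself a hidden failure.

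The size cannot be derived from the article. With 2 to 5 such patients per 20 treated, the gap would be about 9 to 20 percentage points (100% against 91% or 80%). That rests on the assumed counts, on removal of these patients from the denominator, and on no other non-delivery. The conclusion that eligibility and outcome overlap rests on the text alone and needs none of these assumptions. It is worth correcting before enrolment because it affects what the feasibility study can conclude.

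**What to change.** 1. Limit Table 2 to criteria that can be assessed before incision. The preoperative limb of the biopsy item stays, and the untimed deliverability item is restricted to conditions known before incision.
2. List the intraoperative adhesion, biopsy and deliverability findings as reasons for not giving HIPEC, on the model already used for complete resection.
3. Keep every patient with a collected specimen in the turnaround data and every cytology-positive patient in the delivery denominator.
4. Tabulate reasons for non-delivery, with gross peritoneal metastases on a separate line so that delivery can be read with and without them.

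The cost is rewording, one table and a possibly less favourable delivery rate. No patients or procedures are added. The change concerns classification and counting only; no clinical decision about who receives HIPEC changes.

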## Ethical approval and consent to participate

The phase I protocol is to be offered to a single as yet not identified institution. This institution will construct an appropriate consent with the ethics committee/institutional review board. All cytology specimens/human data will be performed in accordance with relevant guidelines and regulations.

## Consent

The participating institution will construct an appropriate consent with the guidance of its ethics committee/institutional review board.

## Research registration unique identifying number (UIN)

Not applicable.

## Data availability statement

Data sharing not applicable to this article as no datasets were generated or analyzed during the writing of the current study protocol.

## Provenance and peer review

Not an invited paper.
